### Interim Analyses

Data will be analyzed at the end of this study.

#### Methods for Additional Analyses (e.g., Subgroup Analyses)

Subgroup analysis will be performed using variables such as geopolitical region, gender, socioeconomic status of parents and care providers, and the levels of education and occupation.

#### Methods in Analysis to Handle Protocol Nonadherence and Any Statistical Methods to Handle Missing Data

The result of this study will be analyzed per protocol. Missing data will be accounted and the proportion with a desirable outcome will be presented.

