## Background and Rationale

Approximately 130 million babies are born annually, about 4 million of these newborns in low- and middle-income countries (LMICs) do not survive beyond the neonatal period (1). More worrisome is the increasing contribution of childhood mortality from the neonatal death. This narrative is not different in Nigeria where neonatal mortality represents one of the highest in the world, only behind India (2).

The reasons for this trend are multifactorial. They vary from ignorance, harsh healthcare workers altitude to caregivers/parents, poverty, the lack of access to good healthcare, the need for spiritual support at a very trying time, and discharged against medical advice (DAMA) (3–7). It is, therefore, important that those who get to a health service be treated holistically, providing physical, psychological, and spiritual support to enable them complete treatment until when discharge is recommended by the treating clinicians (3–5).

Discharged against medical advice occurs when an in-patient decides to leave the hospital before discharge is recommended by the treating clinicians or physicians. DAMA poses serious clinical, ethical, and legal challenges to the individual physician as well as to the hospital (1, 6–9). The DAMA prevalence has been shown to vary depending on geographical areas and the study population. The rate of DAMA compares inversely with the socioeconomic status: a relatively lower rate was observed at a hospital serving primarily middle- and upper-class populations, whereas a higher rate was observed at a hospital serving disadvantaged urban areas (9–13). The pediatric age group, and especially the newborns are at a greatest risk for DAMA in Nigeria from the published literature (9–11).

Discharged against medical advice has been shown to increase the risk of adverse outcomes ranging from medical complications requiring readmission to death (6, 8). Associated outcomes also include higher morbidity, increased mortality, longer hospital stays, and higher costs of treatment when readmitted (10, 11).

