#### Intervention Description

There will be two arms of this study; one arm (the experimental arm) will receive a FBI. The FBI will involve religious counseling encouraging the caregivers/parents to stay in the hospital until their baby is medically discharged. This will also involve offering prayers and reading of holy books for the babies recovery. Each participants will have two to three sessions of the FBI with each session lasting 20–30 min.

The control arm will be exposed to standard of care observed for all babies admitted to a newborn unit.

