### Criteria for Discontinuing or Modifying Allocated Interventions

Participant who also wishes to exit study after due counseling.

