### Outcomes

#### The Primary Outcome

The primary outcome of this study is the retention rate of sick newborns with the FBI in public tertiary hospitals in Nigeria compared with the standard of care.

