	**STUDY PERIOD**							
	**Enrolment**	**Allocation**	**Post-allocation**					**Close-out**
**Timepoint**	** *-t_1_* **	**0**	** *12hs* **			** *72hrs* **		** *t_x_* **

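### Per protocol is the only analysis named and its set is undefined, so outcome-related exclusions can bias the retention comparison, towards the FBI if DAMA families miss sessions more often than retained families.

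*Protocol article*

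**What the plan says.** The section on handling protocol nonadherence and missing data fixes the analysis population in one sentence: "The result of this study will be analyzed per protocol". The next sentence adds only "Missing data will be accounted and the proportion with a desirable outcome will be presented". The article does not mention intention-to-treat, analysis as randomised, or a second population, and it does not say what makes a participant eligible for the per-protocol set.

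Four other statements bear on the point:

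- Outcomes section, main endpoint: "The primary outcome of this study is the retention rate of sick newborns with the FBI in public tertiary hospitals in Nigeria"; the comparator is the control arm.
- Background and Rationale: "Discharged against medical advice occurs when an in-patient decides to leave the hospital before discharge is recommended by the treating clinicians or physicians".
- Intervention Description, FBI arm: "Each participants will have two to three sessions of the FBI".
- Intervention Description, control arm: "The control arm will be exposed to standard of care observed for all babies admitted to a newborn unit".

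The trial is open label.

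**The concern.** The endpoint and adherence are linked, and in one arm only adherence has something to complete. The sessions encourage families to stay until medical discharge, so they belong to the hospital stay. A family that leaves early cuts short its own chance to receive them. If incomplete sessions lead to exclusion, some of the FBI arm's failures leave the analysis because they failed. A control family that leaves at the same moment has missed nothing and stays in.

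The comparison is then between everyone in the control arm and a part of the FBI arm selected after randomisation on something tied to the outcome. In an open-label trial, analysis as randomised is the main remaining protection for the comparison. The authors hope that the result will guide policy, and a positive finding from this analysis could not be told apart from an effect of the exclusions. Because the set is undefined, exclusions could also be settled with arm and outcome known.

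**Working it through.** **Inputs**

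- Total sample 359 and planning DAMA rate 50% (Sample Size). The allocation ratio is not stated; 1:1 is assumed, so 180 and 179.
- Chi-squared or Fisher's exact test, p < 0.05 (Statistical Methods). Sidedness is not stated; two-sided is assumed, so a false claim of benefit for the FBI should occur in 2.5% of trials.
- f = share of FBI-arm DAMA families excluded; g = share of FBI-arm non-DAMA families excluded. Neither is in the documents; both are assumptions and are varied.
- No exclusions in the control arm (assumption: it has no sessions to complete).
- No true effect: DAMA risk p in both arms.

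The plan gives no figure for this bias to reproduce. The total of 359 is taken as it stands. It does not follow from the stated inputs with an assumed 5% margin, since 1.96² × 0.25 / 0.05² = 384.1, but this point does not depend on it.

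**Formulas**

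Share of the FBI arm kept: k = p(1-f) + (1-p)(1-g).

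Per-protocol FBI DAMA rate: p(1-f)/k. With g = 0 this reduces to p(1-f)/(1-pf).

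Probability of a false claim of benefit, pooled two-proportion z test: Φ[(d - 1.96·s0)/s1], where d is the spurious difference, s0 the pooled and s1 the unpooled standard error.

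**f = 0.30, g = 0, p = 0.50**

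- FBI arm: 180 × 0.85 = 153 kept, of whom 180 × 0.5 × 0.7 = 63 are DAMA; 63/153 = 41.2%, so d = 8.8 points.
- Pooled rate (63 + 89.5)/(153 + 179) = 0.459; s0 = 0.0549, s1 = 0.0546.
- (0.0882 - 1.96 × 0.0549)/0.0546 = -0.355, and Φ = 0.36.

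**f = 0.30, g = 0.10, p = 0.50**

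- FBI arm: 63 + 81 = 144 kept; 63/144 = 43.75%, so d = 6.25 points.
- Pooled rate 152.5/323 = 0.472; s0 = 0.0559, s1 = 0.0557.
- (0.0625 - 1.96 × 0.0559)/0.0557 = -0.845, and Φ = 0.20.

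**Range, no true effect**

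| p | f | g | FBI DAMA, per protocol | Bias (points) | False claim of benefit |
|---|---|---|---|---|---|
| 50% | 0 | 0 | 50.0% | 0 | 2.5% |
| 50% | 0.10 | 0 | 47.4% | -2.6 | 7% |
| 50% | 0.20 | 0 | 44.4% | -5.6 | 17% |
| 50% | 0.30 | 0 | 41.2% | -8.8 | 36% |
| 50% | 0.50 | 0 | 33.3% | -16.7 | 85% |
| 50% | 0.30 | 0.10 | 43.75% | -6.25 | 20% |
| 50% | 0.30 | 0.30 | 50.0% | 0 | 2.5% |
| 50% | 0.30 | 0.40 | 53.8% | +3.8 | 0.5% |
| 20% | 0.30 | 0 | 14.9% | -5.1 | 24% |

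Simulation agrees with these rates. When every randomised neonate is analysed in the allocated arm, the simulated two-sided error under the null is 4.9% to 5.1% for p of 10%, 20% and 50%.

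**The case against.** The strongest reply is that the set is undefined. The Intervention Description says what families will receive; it does not set a minimum for entering the analysis, and one session might qualify. This stands: exclusion for incomplete sessions is inferred from the usual meaning of the term and the session schedule. Reading the phrase as merely 'according to the protocol' is unlikely, because a section headed for nonadherence would then say nothing about it.

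A reader might infer three stronger claims, and the documents support none of them.

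- *The bias always favours the FBI.* All newborns with parental consent are eligible, with no minimum expected stay. Babies medically discharged early, babies who die early, and families who decline sessions but stay could also miss sessions. Excluding retained babies pushes against the FBI. That f exceeds g is plausible but not established, and the g = 0 rows are the extreme case.
- *Families who exit the study are lost from the analysis, and only in the FBI arm.* The discontinuation criterion reads "Participant who also wishes to exit study after due counseling". It does not say that data are dropped, and control families may exit too.
- *The participant timeline shows sessions spread over days.* Under "Post-allocation" it has columns for 12 and 72 hours, but the table as read is too broken to place the sessions. The argument needs only that they occur during the stay after allocation.

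The 50% rate is a calculator input, not evidence about these units. At 20% the effect is smaller but remains. None of this defends per protocol as the sole analysis.

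**Conclusion.** The point holds in this form: the article itself commits to per protocol as the only analysis, so this is not a detail left to an analysis plan, and the choice admits outcome-related exclusions into the primary comparison. The direction depends on f and g: towards the FBI if DAMA families miss sessions more often than retained families, none if equally often, away from it if less often. At the protocol's own 50% planning rate, f = 0.30 with g between 0 and 0.10 produces a spurious 6 to 9 points and a false claim of benefit in about 20% to 36% of trials instead of 2.5%. These sizes rest on assumed f and g, 1:1 allocation, a two-sided test and no exclusions in the control arm. Whatever the direction, the per-protocol comparison is no longer a randomised one, and the change should be made before the data are analysed.

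**What to change.** Replace the first sentence of the section on nonadherence and missing data with wording such as: 'The primary analysis includes every randomised neonate in the allocated arm, whatever number of sessions was received. DAMA at any time after randomisation counts as non-retention. Families who stop the sessions remain in the analysis, and discharge status is still collected unless they withdraw consent for the use of their data. A per-protocol analysis is supportive only.' State in the same place which participants form the per-protocol set in each arm. Add a sensitivity analysis that counts missing discharge status as DAMA.

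The cost is one paragraph and two short additional analyses. The article describes the outcome as a single measurement without follow-up, so collecting it for families who stop the sessions should add little work; where it is recorded is not stated. The drawback is that the estimate is diluted by families who leave before receiving sessions.

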#### Plans to Give Access to the Full Protocol, Participant Level-Data, and Statistical Code

The protocol shall be published in a peered review journal and made publicly accessible to interested individuals or body.

Individual patient data will be de-identified and stored to be encrypted in a passworded computer. De-identified data will also be stored in highly secured cloud computing. The participant level-data set and statistical code shall be made available after following due process adhering to good ethical standard.

### Sharing Time Frame

The de-identified data will be publicly available for 2 years on the trial website.

#### Key Access Criteria

Open access to de-identified data set, which can be used for any analysis related to DAMA.

### Oversight and Monitoring

#### Composition of the Coordinating Center and Trial Steering Committee

A trial steering committee consists of the Principal Investigator, two scientific enquirers, the public enquirer, and a biostatistician. They will meet frequently to provide an oversight function for the trial conduct over the two centers in the country.

Each center will have a hospital trial group headed by a consultant pediatrician, who will be saddled with running daily events in the hospital, providing organizational support, and reporting on a weekly basis to the steering committee.

#### Composition of the Data Monitoring Committee and Its Role and Reporting Structure

The data monitoring committee consists of the Head of the Information Technology at the University College Hospital Ibadan. He will centrally manage the database. He will be supported by two assistants if he is unable to perform his duties. They will be responsible for entering the data from the UCH center to the database. The head will give access to focal persons (information technologist) at the collaborating centers in Nigeria. These individuals will be responsible for entering the data into the central database in UCH. Regular zoom meeting will be held among the group members to address pressing issue. The data monitoring committee shall be independent of the core trial committee.

### Adverse Event Reporting and Harms

The trial is asocial intervention. If any instance of abuse is reported by the participant, they will be handled on case by case bases by the steering committee.

#### Frequency and Plans for Auditing Trial Conduct

The local ethics board will monitor the progress of this trial, and all medications and update will be relayed to the body as events unfold.

#### Plans for Communicating Important Protocol Amendments to Relevant Parties (e.g., Trial Participants and Ethical Committees)

Any modification to the protocol or trial update will be communicated to the Ethical Approval bodies, Trial Registry, and any other relevant parties.

### Dissemination Plans

The outcome of this study will be communicated to participants, ethics board, and healthcare professionals. It will be published in peer-reviewed scientific journals for public access. Data will be made available to the public maintaining ethic guidance.

## Discussion

The outcome of this analysis will give insights into the effectiveness of FBI on DAMA. It will also predict the effect of the mediators of parents/caregivers religiosity, spirituality, forms of FBI, the religious sect of parents/caregivers, and social support on the rate of DAMA on neonatal admission in tertiary hospitals in Nigeria. This could help Public Health Institutions and Governments make decisions about the determinants of neonatal DAMA and how to mitigate such outcomes. It is hoped that the evidence from this study may guide policy formulation and guidelines on enhancing hospital retention of sick neonates until they are fit for discharge.

## Ethics Statement

The studies involving human participants were reviewed and approved by ethical approval was obtained from the State Research Ethics Review Committee (Ref:AD13/479/3047A) and the trial was also registered (PACTR202102670906630). Written informed consent to participate in this study was provided by the participants' legal guardian/next of kin.

## Abbreviations

RCT: Randomized clinical trial
PACTR: Pan Africa Clinical Trial Registry
FBI: Faith-based intervention
LMIC: Low- and middle-income countries.
